## Abstract

**Introduction:**

Dental implants are a widely accepted solution for tooth replacement, but standardised outcome assessment, particularly patient-reported outcomes, remains limited. Moreover, international variability in implantology practices underscores the need for consistent and comprehensive evaluation tools. This study aims to develop and validate the DEntal implaNt Set (DENS), a standardised tool to capture clinician and patient perspectives on peri-implant health and restorative treatment outcomes.

**Methods and analysis:**

This prospective multicentre cohort study aims to include 1000 patients aged 18–75 years from 30 dental practices in the Netherlands and Spain. The DENS was developed by an international multidisciplinary team through structured iterative working sessions, grounded in the mandatory outcome domains of the Implant Dentistry Core Outcome Set and Measurement (ID-COSM) framework and informed by expert consultation with the ID-COSM authors. Patient-reported outcome measure (PROM) items were adapted from validated instruments and subjected to forward-backward translation into Dutch, English and Spanish. Data are collected at six time points from pre-implant placement to 12-month follow-up. Clinical outcomes and PROMs are assessed via the digital. Descriptive analyses and psychometric testing of the DENS instrument are planned at the end of the data collection phase.

**Ethics and dissemination:**

Ethical approval was granted by committees in the Netherlands (Erasmus University Medical Center: MEC-2023-0688; Anna Hospital Eindhoven: 2024.076; Anna Hospital Geldrop: MEC-24.008; St. Antonius Hospital: R&D/Z24.070/DENS; University Medical Center Groningen: METc 2024/389) and Spain (CEI-SL 2024/122). Participants provide informed consent, and no procedures exceed standard clinical care. All data are pseudo-anonymised. Findings will be shared through publications, conferences and professional networks. The DENS tool will be made available for clinical practice and research purposes to promote standardised, evidence-based practice in implant dentistry.

**Trial registration number:**

NCT07337057.

Strengths and limitations of this studyInternational standardisation uses the Implant Dentistry Core Outcome Set and Measurement framework that identifies essential outcome domains for standardised measurement instruments for both patient and clinician perspectives.Multilingual validation follows professional translation methodology.Longitudinal tracking of at least 12-month systematic follow-up.Limited scope covers only two countries with 12-month follow-up.Implementation challenges include research-engaged practice bias and complex questionnaire administration.

## Background and rationale

 Tooth loss represents a significant global health challenge affecting individuals across all age groups, from young adults to the elderly. The extent of tooth loss varies considerably, ranging from single-tooth defects to complete edentulism. Multiple aetiological factors contribute to tooth loss, including dental trauma, caries, periodontal disease, oral malignancies and other pathological conditions.^1^

Since its initial description in the 1960s, dental implant therapy has evolved to become the gold standard treatment for tooth replacement and in case of functional denture problems. Dental implants are currently used for single-tooth replacement with crowns, multiple-tooth replacement with bridges and in edentulous patients with full dentures supported by implants. The decision to place a dental implant following tooth loss depends on multiple factors, including cost, longevity, oral and general health and the availability of alternative treatment options. This decision-making process is guided by country-specific clinical guidelines and protocols, if available, which can result in variations in indications and treatment approaches in implantology across different settings and even across different practitioners.^1–3^

Most studies in implant dentistry focus on clinical outcomes, such as implant success and survival rates, presence of dental plaque, bleeding on probing (BOP), probing pocket depth, bone loss, peri-implantitis and aesthetic assessments such as the Pink Esthetic Score and the White Esthetic Score.^4–6^ However, limited attention has been paid to the patient’s perspective. Recently, there has been growing emphasis on patient-reported outcome measures (PROMs) in implantology. In response, the International Team for Implantology (ITI) has formed a working group dedicated to developing core domains from the patient perspective.^7^ Nevertheless, to date, no standardised methods or validated questionnaires exist to systematically assess implant outcome, either from the patient perspective or from the clinical standpoint.

A standardised set of PROMs and clinician-reported outcome measures (ClinROs) would enable the implementation of uniform research within the field of implantology. In developing such a set, it is essential to identify which domains and instruments are most relevant and clinically meaningful to implantology. Recently, Tonetti *et al* published a consensus statement that describes the core domains for developing a core outcome set in implant dentistry. This set focuses on both clinical outcomes and patient-reported outcomes.^8^ Although this set was originally developed for research purposes, the domains might be highly relevant in clinical practice too.

In developing and implementing such a set, it is essential to account for the previously discussed international differences in implantology practices and language. Therefore, establishing this set through international collaboration is crucial to ensure appropriate cross-cultural validation. Furthermore, it is important to investigate the extent to which these core domains can be applied in clinical practice using validated questionnaires targeting both patients and healthcare professionals. If this set proves to be implementable in clinical practice, it will constitute a significant advancement by facilitating the systematic evaluation of implant care, both in routine clinical application and in standardised research at national and international levels. A validated and reliable outcome set would support clinicians in assessing, monitoring, improving, differentiating and benchmarking their clinical performance.

## Aim

The aim of this protocol is to describe the development and implementation of the DEntal implaNt Standard set (DENS), a standardised outcome measurement instrument comprising ClinROs and PROMs, based on core-domains of the Implant Dentistry Core Outcome Set and Measurement (ID-COSM) framework, for evaluating peri-implant health and restorative outcomes in routine implant dentistry practice across two countries.

Formal psychometric validation of the DENS instrument is planned as a subsequent step following completion of data collection.

Following psychometric validation, the DENS instrument will be made available to support in clinical practice and research settings internationally.

## Material and methods

### Overall study design

The project is a prospectively designed multicentre cohort study and aims to include patients from 20 dental practices in the Netherlands (coordinated by Erasmus University Medical Center, Rotterdam) and Spain (coordinated by University of Santiago de Compostela). From the dental practices, 1000 consecutive patients are included within 24 months. ClinROs and PROMs are systematically collected at multiple timepoints throughout the treatment protocol, including baseline, implant placement, integration phase and restorative outcomes.

Patient enrolment commenced on 1 June 2024 in the Netherlands and on 1 October 2024 in Spain. Data collection is projected to be completed by 1 June 2028.

### Establishment of the research team

A multidisciplinary working group comprising implantologists, prosthodontists and researchers from the Netherlands and Spain was established to develop a comprehensive outcome measurement set. The international team represented three academic centres: Erasmus University Medical Center (Rotterdam, the Netherlands), the University of Santiago de Compostela (Madrid, Spain) and the University Medical Center of Groningen (Groningen, the Netherlands), ensuring diverse clinical perspectives and cultural considerations.

### Development of the preliminary DENS

The DENS was developed by an international multidisciplinary team, based on the five mandatory outcome domains established by Tonetti *et al* through the ID-COSM initiative.^8^ These domains were identified through a rigorous international consensus process comprising systematic reviews, patient focus groups and a three-round Delphi survey, providing the evidence-based foundation for standardised outcome measurement in implant dentistry.

Given that the ID-COSM mandatory outcome domains had already been established through an international consensus process, a new Delphi procedure for domain selection was not considered necessary. Instead, item selection and refinement were conducted through structured expert working sessions within the international research team.

Building on these domains, candidate questionnaire items were drawn from validated instruments: the Oral Health Impact Profile (OHIP-14), OHIP-EDENT, the Psychosocial Impact of Dental Aesthetics Questionnaire (PIDAQ), the Dental Satisfaction Questionnaire (DSQ) and the Patient Satisfaction Questionnaire (PSQ).^9–13^ Items were selected and refined through multiple iterative working sessions with the core research group across three academic centres and evaluated against three criteria: (1) clinical relevance to routine implant dentistry practice, (2) direct alignment with an ID-COSM mandatory outcome domain and (3) comprehensibility and respondent burden for both clinicians and patients. Items considered overlapping, redundant or insufficiently specific to the implant dentistry context were excluded through team consensus. The preliminary item set was subsequently presented to the authors of the ID-COSM report for expert review, and their feedback was incorporated into the final instrument.

Questionnaires were then professionally translated into Dutch, English and Spanish using forward-backward translation methodology to ensure linguistic and cultural equivalence across both study countries. The present multicentre prospective cohort study constitutes the implementation phase, during which the DENS is administered under clinical conditions. Formal psychometric validation, including assessment of internal consistency (Cronbach’s α), structural validity and construct validity in accordance with COnsensus-based Standards for the selection of health Measurement INstruments (COSMIN) methodology, is planned at the end of the data collection phase and will be reported in a separate publication.

### DENS domains

The ID-COSM report by Tonetti *et al*^8^ identified the core outcome domains essential for developing standardised measurement instruments, providing the foundational framework for both clinician-reported and patient-reported outcomes in implant dentistry. The current project adheres to these domains to enhance the consistency and quality of research, ultimately advancing evidence-based implantology and optimising patient care.^8^ The DENS will include both patient-reported outcomes and clinician-reported outcomes, based on the following key domains:

Surgical morbidity and complications (until delivery of final prosthesis).Peri-implant tissue health status.Intervention-related adverse events (including implant/prosthesis loss—after delivery of final prosthesis).Complication-free survival (implant/prosthesis related).Overall patient satisfaction and comfort.

### Clinical-reported outcomes measures

The ClinROs include baseline patient characteristics. The following case-mix variables are collected: age, gender, oral hygiene practices (eg, tooth brushing frequency, interdental cleaning), dental visits in the past year, tobacco use status (current smoker, former smoker, non-smoker), alcohol consumption (daily vs occasional) and chronic medical conditions (eg, diabetes, hypertension).

In line with the mandatory domains of the ID-COSM, additional clinical variables are assessed at each visit. These include:

Periodontal health, using the Periodic Periodontal Screening score at the implant site and neighbouring teeth.BOP.Occurrence and timing of complications following implant placement throughout the 12-month follow-up period.

At the time of implant placement, the following data are also collected:

Implant details (brand, type).Type of implant-supported restoration, including:Single-unit fixed dental prosthesis (screw-retained or cemented).Multi-unit fixed dental prosthesis.Removable partial denture.Removable full denture.

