**Figure 1 F1:**
[figure not shown]
Overview of DENS follow-up.

All patients aged 18–75 years who have an indication for implant-supported fixed single-tooth or multiple-tooth replacement or implant-supported removable prosthesis are eligible to be enrolled in this study by their treating clinician/dental practice. This study will also include patients that require minor bone augmentation or soft tissue grafts.

Inadequate oral hygiene, low digital literacy, major bone-augmentation procedures (extra-oral donor sites), pregnancy, a history of radiotherapy in the head and neck region and language barriers are reasons to exclude patients from the study population.

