## Discussion

This protocol describes the development of DENS, a standardised outcome measurement instrument combining ClinROs and PROMs for routine dental implant practice. Within implant dentistry, there is currently no consensus on how to systematically measure and report treatment outcomes, particularly from the patient perspective. This lack of standardisation limits cross-study comparisons, evidence synthesis and the ability to benchmark clinical performance across settings and countries. The DENS addresses this gap by operationalising the mandatory outcome domains of the ID-COSM framework^8^ into a practical, multilingual instrument applicable to both clinical practice and research.

The clinical relevance of systematic PROM collection in implantology is well supported. Patient-reported outcomes have been shown to effectively predict treatment success and identify key risk factors for postoperative complications, including patient-related factors such as age and alcohol consumption, and surgery-related factors such as pain perception and bone augmentation procedures.^18^ Structured collection of these outcomes enables clinicians to identify high-risk patients, support targeted interventions and contribute to evidence-based quality improvement. By enabling international benchmarking of both clinical and patient-reported outcomes, the DENS has the potential to advance implant dentistry through robust comparative research and standardised quality assurance.

The DENS was developed through international collaboration across three academic centres, building directly on the ID-COSM domains rather than initiating a new consensus process, given the rigorous foundation already established by Tonetti *et al*.^8^ Items were drawn from validated instruments, refined through iterative expert working sessions and reviewed by the ID-COSM authors prior to finalisation. Forward-backward translation into Dutch, English and Spanish ensures cross-national applicability and enables outcome comparability across diverse patient populations and healthcare settings.

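### Alcohol is coded with no level for non-drinkers, and restoration type is listed only at implant placement, before the prosthesis exists; whether augmentation and grafting are recorded should also be confirmed.

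*Protocol article*

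**What the plan says.** All variable lists are in the protocol article, section Clinical-reported outcomes measures.

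- **Case-mix list.** It opens with "The following case-mix variables are collected: age, gender, oral hygiene practices" and goes on to dental visits, tobacco, alcohol and chronic conditions. Alcohol is given as "alcohol consumption (daily vs occasional"; tobacco as "tobacco use status (current smoker, former smoker, non-smoker".
- **Data at implant placement.** "At the time of implant placement, the following data are also collected" introduces a short list: "Implant details (brand, type).Type of implant-supported restoration, including" four kinds of fixed or removable restoration. For single-unit restorations the means of retention is also given.
- **Who is enrolled.** The eligibility section says: "This study will also include patients that require minor bone augmentation or soft tissue grafts".
- **Risk factors named.** The Discussion, reporting a cited study, lists "patient-related factors such as age and alcohol consumption, and surgery-related factors such as pain perception and bone augmentation procedures".
- **Planned use.** Statistical methods plans to assess construct validity through associations of patient-reported scores with clinical outcomes and case-mix variables, and to send practices aggregated summaries for benchmarking.
- **Visit order.** Data collection procedure puts the visits before prosthesis placement and at 3 and 12 months after it later than implant placement, with clinician and patient forms at every time point.

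**The concern.** The alcohol levels are a written coding rule, not a detail lost in condensing. Followed as written, the rule has no place for a patient who does not drink. Such a patient is either counted as an occasional drinker or has no value and cannot enter any association with alcohol. The resulting contrast then depends on how many non-drinkers there are. If that share differs between the Netherlands and Spain, the same code means different things in the two countries.

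Restoration type raises a separate question of timing. What is written down at implant placement is the intended restoration. The questionnaire later asks about the fit, appearance and cleaning of the crown, bridge or prosthesis. Grouping those answers by the recorded type groups them by intention rather than by what the patient received.

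The third matter is smaller. Patients needing minor augmentation or grafts are enrolled, augmentation is named as a risk factor, and surgical morbidity is the first DENS domain, yet neither list shows an item for augmentation or grafting.

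**Working it through.** **1. The plan's own numbers.** Sample size gives 15 practices per country, two countries, 30 to 50 patients each and a 70% response.

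- Included: 2 × 15 × 30 = 900 and 2 × 15 × 50 = 1500.
- End of follow-up: 0.70 × 900 = 630 and 0.70 × 1500 = 1050.

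Both ranges agree with the protocol. They are not in dispute and serve only as denominators.

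**2. Patients without a valid alcohol level.** The documents give no share *s* of non-drinkers, so a range is assumed.

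| s (assumed) | of 630 | of 1050 |
|---|---|---|
| 10% | 63 | 105 |
| 30% | 189 | 315 |
| 50% | 315 | 525 |

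**3. What the coded contrast estimates if non-drinkers are pooled with occasional drinkers.** Let *d* be the share of daily drinkers. The pooled group then has size 1 − d, of which a fraction w = s/(1 − d) does not drink. The coded difference is

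(daily − occasional) + w × (occasional − none).

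For illustration, assume complication risks of 10% (none), 15% (occasional) and 20% (daily), with d = 10%. None of these figures is in the documents.

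| s | w | daily − pooled, in percentage points |
|---|---|---|
| 10% | 0.10/0.90 = 0.111 | 5 + 0.111 × 5 = 5.6 |
| 30% | 0.30/0.90 = 0.333 | 5 + 0.333 × 5 = 6.7 |
| 50% | 0.50/0.90 = 0.556 | 5 + 0.556 × 5 = 7.8 |

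The contrasts with a plain meaning are daily versus none (10 points) and daily versus true occasional (5 points). The coded one equals neither. It moves by 2.2 points across the assumed range although no underlying risk has changed. The same algebra applies to mean scores.

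**4. Restoration type.** Clinical-reported outcomes measures lists it among the data taken at implant placement. Data collection procedure places the prosthesis stage later. The recorded value can therefore only be the planned type, and no later confirmation is listed. The Discussion's section on implementation feasibility adds that Dutch patients frequently go back to their general dentist after implant placement, so the implant practice may not itself see what is delivered. The documents give no figure for how often planned and delivered types differ.

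**5. Augmentation and grafting.** The eligibility section admits minor procedures, the Discussion names augmentation as a risk factor, and neither the case-mix list nor the placement list has an item for it. This shows absence from the article's lists and no more.

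**The case against.** The strongest reply has five parts.

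- **Alcohol may be shorthand.** The article may have shortened the levels, and if non-drinkers are filed under *occasional*, the variable still separates daily drinkers from everyone else. The second part is true, and it limits the loss to the contrast between none and occasional. The first part is possible, but the tobacco levels in the same list are written out with a level for none. The alcohol rule has to be read as it stands. Alcohol is also one of seven listed case-mix variables and not an outcome.
- **Adjustment.** A reader might infer that the named risk factors cannot be adjusted for correctly. The documents do not support that: Statistical methods states associations and descriptive summaries, with no adjustment model, and the study calls itself exploratory.
- **Restoration type as a risk factor.** A reader might also count it among the risk factors that the Discussion names. It is not there. The point is one of timing only, and the interval between implant and prosthesis is not stated.
- **Augmentation.** A reader might conclude that the data form has no such field. The form is not shown and an article condenses the full protocol, so a field may well exist. Major augmentation from extra-oral donor sites is excluded in any case. What remains is a query.
- **Irreparable loss.** Statistical analysis alone cannot recover unrecorded values, but dental records and later forms can supply much of them, so the loss is not permanent.

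**Conclusion.** The point holds in a limited form. The alcohol coding as written is defective. It has no level for non-drinkers, and it feeds an analysis that the protocol plans, on a factor that the protocol itself connects with complications. Its size cannot be fixed from the documents. The counts and the 5.6-to-7.8-point movement rest wholly on assumed shares and risks; they show the direction and mechanism, not an expected bias.

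Restoration type, as listed, is the planned type. This matters for grouping answers about the prosthesis to the extent that planned and delivered types differ, which is unknown.

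The augmentation and graft item is a real tension between eligibility, Discussion and the variable lists, and calls for confirmation rather than a finding of omission.

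**What to change.** 1. **Alcohol.** Code it as none, occasional or daily. For patients already enrolled, ask on a remaining follow-up form about drinking at baseline, or check the record. Code the rest as unknown, separately from *occasional*. Data collection is projected to run to 1 June 2028, so follow-up forms should remain for many patients.
2. **Restoration type.** Keep the entry at implant placement, labelled as planned. Confirm the delivered type on the existing 3-month clinician form, and use the delivered type when grouping answers on fit, appearance and cleaning.
3. **Augmentation and grafting.** Confirm that the platform records both. If it does not, add a yes/no field for each, filled from the dental record.

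The cost is a few short fields in the survey platform and a brief record check, with no change to treatment. The downside is that some alcohol values will stay unknown, and baseline drinking asked for later relies on recall.
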